##### Recruitment of Participants

Convenience sampling will be used to recruit participants for both co-creation trajectories. A first strategy will be to reach out to children via schools in the city of Ghent and to contact their grandparents (via their parents). All of the children of the first and the second grades (classes 1–4 of primary school) of 2 schools will receive an information letter about the goal of the study and some explanation about the co-creation trajectories. In the case that this results in too few respondents, additional schools will be contacted. If both children and their grandparents are interested in participating (parents must ask the grandparents), they can fill in their contact information using a paper strip attached to the information letter. Of those who respond with interest in joining, a researcher will call the parents and grandparents to ask some questions regarding the sociodemographic characteristics (i.e., age and gender) and inclusion criteria (i.e., language and physical, cognitive, and psychological health status) of the grandchildren and grandparents. A group of 12 grandchildren and 12 grandparents will be chosen by purposive sampling, which means that a researcher will choose the participants based on these characteristics/criteria so as to better represent the population during the co-creation trajectories. In regard to age, both younger and older grandchildren and grandparents will be chosen. In regard to gender, there will be a mix of boys and girls and grandmothers and grandfathers.

Before participating in the co-creation trajectories, each participant will be asked to sign an informed consent. Grandchildren will need parental consent, as well as their own informed consent; grandparents will sign an informed consent for themselves. Grandchildren and grandparents will be asked to bring these signed forms to the first co-creation session that they attend.

##### Content of the Co-Creation Trajectories

Co-creation Trajectory 1: Development of the Intergenerational movement program.

*Session 1 (grandparents):* In this session, researchers and grandparents will meet each other. A short introduction about the intergenerational movement program will be given. Grandparents will be asked to write down movement activities that they would like to do (and not like to do) with their grandchildren. The barriers and motivators will be determined, which will be the implementation of Step 4 of the theoretical framework. COM-B (i.e., capability, opportunity and motivation of behavior) and the TDF (i.e., Theoretical Domains Framework) will be examined in order to obtain a better overview of their ability and potential (e.g., ‘Do you feel you have enough skills to exercise together with your grandchild? Why or why not?’) and the barriers and facilitators (e.g., ‘Does the environment offer sufficient opportunities to be active together? Why or why not?; ‘Do you have sufficient time to exercise together? Why or why not?’; ‘Are you able to sum up some advantages to being physically active together with your grandchild?’). 

*Session 2 (grandchildren):* In this session, the same structure will be used as that used in the first session with grandparents. The biggest difference between the two sessions will be that, in this session, the information will be obtained by playing games and making metaphors to motivate the children during the sessions, and a mascot—a kangaroo with a child in its pouch—will be used. A kangaroo was chosen because they are quite active animals, and it will represent the grandparent with the grandchild.

After these two sessions, the intervention goals will be established/refined by the project researchers based on the barriers and motivators expressed by the grandchildren and grandparents. Furthermore, the intervention functions will be considered and selected based on Step 4 of the BCW. Both intervention goals and functions will be discussed with the grandparents; only intervention goals will be discussed with the grandchildren in the following co-creation sessions. 

*Session 3 (grandparents):* In this session, first a summary of Sessions 1 and 2 will be given. Grandparents will be able to give their input and feedback on the proposed intervention goals and intervention functions, which is Step 5 of the BCW. Second, the ideal movement session will be explored. More specifically, **content** and **format** (e.g., working on a theme, the specific topic per session, game format or exercises, everything being done together or being split between grandchildren and grandparents); **frequency** and **duration** (e.g., how many hours and how many times per week); **intensity** and **environment** (e.g., cardio, balance, coordination, a combination of both, high sweat production, indoor or outdoor, in a green or urban area) will be examined. Finally, we will explore which movement activities the grandchildren and grandparents can do together at home in addition to the sessions. Researchers will give some examples, and grandparents will be asked to give their opinions (e.g., pedometer, treasure hunt, challenge: goalsetting for taking more steps/day, games, using an app for workouts, going online to do exercises together via Zoom). In addition, grandparents will be asked how they can be **motivated** to participate in the sessions to keep participation rates high. 

*Session 4 (grandchildren):* In this session, the same structure will be used as in the third session with the grandparents. As in the previous session with the grandchildren, information will be obtained in a more informal way, using games, photos, and interactions with each other. Some of the elements that were explored in the session with the grandparents (e.g., intervention functions, frequency, and duration of the sessions) will not be discussed with the grandchildren because that would be too difficult for them. 

After these 4 sessions, a movement session will be prepared by the project researchers and movement scientists based on the input and feedback from Sessions 1–4.

*Session 5 (both groups):* In the last session, grandchildren and grandparents will be brought together. A movement session characteristic of the program will be presented to them. Some exercises will be tried out, and grandchildren and grandparents will be asked a few questions about attractiveness, feasibility, fun, motivation, and co-PA. At the end, they will fill in a SWOT analysis to determine the strengths, weaknesses, opportunities and threats that they associated with the exercises. 

*Co-creation Trajectory 2: Cognitive enrichment of the intergenerational movement program*. This co-creation trajectory will follow the same order and procedure as described for the first co-creation trajectory, but the information that was already obtained will be included here, and it will not be collected again. Therefore, it is expected that only three sessions will be needed in order to develop the cognitively enriched intergenerational movement program. 

*Session 1 (grandparents):* In this session, the activities that were performed and the most important findings from the previous co-creation trajectory will be explained. Furthermore, the objectives of this trajectory and the expectations will be clarified. The main goal is to find out which cognitive movement activities they found to be attractive and feasible for inclusion in this program. An introduction to PA and cognitive functioning will be given, and researchers will also provide some examples of cognitively enriched movement activities. The desired duration and challenge of the activities will be ascertained. From the literature, it is known that a combination of PA and cognitive functioning must last at least 10 minutes to observe effects, so this will be taken into account. 

*Session 2 (grandchildren):* This session will have the same content as the session with the grandparents. A big difference will be that the desired duration and challenge will not be ascertained from the children. Furthermore, everything will be explained in an understandable way for them. More examples of cognitively enriched movement activities will be provided to the children as developed by both the researchers and the grandparents (from Session 1). 

*Session 3 (both groups):* As in the previous co-creation trajectory, grandchildren and grandparents will be brought together, and the cognitively enriched movement activities for the intergenerational movement program will be tested out. Grandchildren and grandparents will be asked a few questions about attractiveness, feasibility, fun, motivation, and co-PA. At the end, they will be asked to fill in a SWOT analysis to determine the strengths, weaknesses, opportunities and threats that they associated with the exercises. 

##### Process Evaluation Co-Creation

After each co-creation session, participants will be asked to fill in a short questionnaire to evaluate how the session was perceived (i.e., ‘How do you feel at this moment?’; ‘Would you give/not give your opinion during the session, and why?’; ‘Did the environment feel safe for you, and why?’; ‘During which portion, or with which aspect, did you feel uncomfortable during the session?’; ‘Which aspects of the session were fun for you, and which aspects were boring?’; ‘Which aspects caused you to be motivated to do something?’; ‘Why did you take part (or not take part) in conversations?’). They will also be able to add suggestions for the next sessions (i.e., ‘Can you add some suggestions for the next session(s)? What could be improved? What should be different?’). 

##### Expert Meeting 

At the end of Co-creation Trajectories 1 and 2, an elaborated series of activities will be prepared by movement scientists, after which an expert meeting will be organized with experts in movement activities and cognition in children and older adults in order to obtain additional advice about the proposed activities (e.g., ‘What is important in some specific exercises?; What is the correct body posture?; Which elements are important for motivation or persistence in something?’). An observer will write down the most important findings. 

Evaluation of the intervention

#### 2.2.2. Pilot Study

After the two co-creation trajectories are finalized, a pilot study will be conducted to determine whether the two different programs are attractive, feasible, and fun for grandchildren and grandparents (see Figure 1). The purpose of this portion of the study will be to finetune the programs and recruitment strategies to optimize the RCT. There will be 2 groups of 12 dyads. Group 1 will engage in the intergenerational PA program, while Group 2 will engage in the cognitively enriched intergenerational PA program. Each session will be led by researchers and facilitators (with a background in movement and sports sciences and/or health promotion research). All the sessions will take place in Ghent (i.e., where the main researchers are based); the exact location will depend on the preferences of the participants and what is practically feasible.

##### Participants and Sample Size

Similar inclusion criteria will be used to recruit participants for the pilot study as those used for the co-creation trajectories. (See Participants and Sample Size Part in Section 2.2.1) The required sample size for a pilot study is between 30 and 50 participants [59]. Therefore, and also taking into account a group size where safety can be guaranteed, two groups of 12 dyads will be recruited (i.e., in total, about 24 grandchildren and 24 grandparents; 12 grandchildren and 12 grandparents per group, including the participants of the co-creation sessions), assuming an attrition rate of 30% (7 dyads) [61], and guaranteeing a sufficiently large group size for the sessions. A projected attrition rate of 30% instead of 20% has been chosen because we have taken into account that, if one grandchild or grandparent drops out, this implies that the whole dyad will be excluded from the study. Therefore, 2 groups of 12 dyads will be recruited (a total of about 24 grandchildren and 24 grandparents). (See Figure 4).

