#### 2.1.2. Co-Creation

A lot of interventions are developed using a deficit-based approach, where researchers use their knowledge to implement a general program for the participants. However, it has been shown that developing an intervention without taking the needs and requirements of the target population into account results in higher drop-out and lower participation rates for the program [49,50]. A design process in which end-users are engaged in the development process is called a co-creation design. It is a co-construction between researchers, end-users (i.e., grandchildren and grandparents), and stakeholders (i.e., experts in movement sciences and organizations) with the aim of tailoring the program to the target group. Co-creation has received more attention in recent years to enhance effectiveness and to prevent drop-out in (health promotion) interventions [51,52,53,54]. A co-creation design will be specifically used to empower grandchildren and grandparents, to learn what kind of activities they would like to do in the program, to learn what their ideal program looks like, and to keep fun levels and motivation and participation rates high in order to make the intervention effective and to obtain implementation success. More detailed descriptions of the co-creation trajectories and sessions are presented below. 

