### 2.2. Methods

#### 2.2.1. Co-Creation

##### Participants and Sample Size

Similar inclusion criteria will be applied for participation in both trajectories (intergenerational PA and intergenerational cognitive enrichment). Grandchildren will be 6 to 10 years old; grandparents will probably be aged between 60 and 75, but their age will depend on the age of the children. This age range for the grandchildren has been chosen because, in Flanders, the majority of children in this age category fail to reach the guidelines for PA; only 6.5% of the 6–9-year-old children have an adequate PA level [56]. Furthermore, interventions to promote PA in this age group can be improved to sustain longer-term effects [57], and young children are still influenceable, which makes it advantageous to include them in this intervention. In addition, it is a good age range for choosing appropriate work formats for the co-creation sessions, and grandparents of children in this age group are normally still physically able to participate in a movement program. To explore what grandmothers and grandfathers like, both genders will be recruited in the co-creation sessions. Inclusion criteria for the grandchildren include: an age between 6 and 10 years old; the possession of at least 1 grandparent; the ability to speak Dutch; and the lack of any serious physical, cognitive, or psychological health problems. Inclusion criteria for the grandparents include: the possession of at least 1 grandchild (6–10 years old), the ability to speak Dutch; and the lack of any serious physical, cognitive, or psychological health problems. 

Each co-creation trajectory will include 12 grandchildren and 12 grandparents, according to Leask’s recommendations for sample sizes in co-creation activities [58]. (See Figure 4).

Study Design and Numbers of Participants

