##### Participants and Sample Size

The same inclusion criteria will be used for the RCT as in the co-creation trajectories and the pilot study (i.e., speaking Dutch; having at least one grandparent or grandchild; and having no serious physical, cognitive, or psychological health problems). Based on effect sizes of intergenerational programs of children and older adults, an effect size of 0.15 will be intended for the outcomes of PA, cognitive functioning, psychosocial well-being, and quality of the family relationship [65]. The required sample size has been calculated using the software GPower 3.1.9.7 (Universität Düsseldorf, Düsseldorf, Germany) [60]. The sample calculation will be based on 80% power to detect a significant difference in PA, cognitive functioning, psychosocial well-being, and quality of the family relationship between groups and over time. Significance level alpha 0.05, having 3 groups (2 intervention groups and 1 control group) and 3 measurements (pre-, post-, and follow-up). A priori power analysis for the RCT suggests a total sample size of around 45 dyads (*n* = 90 grandchildren and grandparents). Assuming an attrition rate of 20% [61], a total sample size of 54 dyads (*n* = 108 grandchildren and grandparents) will be required for the 3 groups. (Each group consists of 36 participants: 18 grandchildren and 18 grandparents). See Figure 4.

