##### Recruitment of Participants

According to the evaluation of the recruitment strategy of the co-creation sessions and the pilot study, the best way to recruit the target population will be chosen based on convenience sampling. The strategies and procedures for the recruitment are described above in the discussion of the recruitment for the co-creation trajectories and pilot study. The first strategy will be the recruitment of grandchildren and their grandparents via schools in (the neighborhood of) Ghent. The second strategy will be via GRAY and their partners. A combination of both strategies is also possible if needed to achieve the desired number of participants.

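### Co-creation participants are counted into the pilot that judges the programme's appeal, and no stated RCT rule keeps dyads from either stage out of randomisation

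*Protocol article*

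**What the plan says.** **Co-creation.** Section 2.1.2 describes the method: "It is a co-construction between researchers, end-users (i.e., grandchildren and grandparents), and stakeholders". In section 2.2.1, "Each co-creation trajectory will include 12 grandchildren and 12 grandparents", and there are two trajectories. The article does not say whether the same people follow both. In the joint closing session of trajectory 1, "Some exercises will be tried out, and grandchildren and grandparents will be asked a few questions about attractiveness, feasibility, fun, motivation, and co-PA"; trajectory 2 closes in the same way.

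**Pilot.** Section 2.2.2 gives the aim: "a pilot study will be conducted to determine whether the two different programs are attractive, feasible, and fun for grandchildren and grandparents". It adds: "The purpose of this portion of the study will be to finetune the programs and recruitment strategies to optimize the RCT". Under Participants and Sample Size, the two groups consist of "12 grandchildren and 12 grandparents per group, including the participants of the co-creation sessions". Each group receives about six sessions of one of the two programmes, and CANTAB, the accelerometers, the diary and the questionnaires are tried out.

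**RCT.** Section 2.2.3, Participants and Sample Size: "The same inclusion criteria will be used for the RCT as in the co-creation trajectories and the pilot study". It names Dutch language, having a grandparent or grandchild, and absence of serious health problems. On recruitment, "The strategies and procedures for the recruitment are described above in the discussion of the recruitment for the co-creation trajectories and pilot study", and the route is to be chosen after evaluating recruitment in the two earlier stages. Appendix A, item 4, describes the RCT school approach in nearly the same terms as section 2.2.1 does for co-creation. The control group receives no intervention. Neither the RCT sections nor the limitations in section 4.2 mention previous participation.

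**The concern.** There are two linked problems.

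First, the pilot is partly answered by the people who shaped what it tests. Someone who chose the activities, tried them, rated them and stayed for a second phase is likely to enjoy them more and find them more feasible than a family new to the project. A place filled from co-creation also gives no information on how well pilot recruitment works. Those results steer the content of the RCT sessions and the RCT recruitment route.

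Second, the RCT criteria as stated admit a dyad that has already had part of one RCT programme and has practised the RCT's own outcome measures. Placed in the control arm, such a dyad is not untreated. Placed in the other active arm, it blurs the comparison of Arm 1 with Arm 2. Prior exposure cannot be undone after randomisation, and a trial of 54 dyads has little slack.

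**Working it through.** **1. Pilot arithmetic.** Inputs from section 2.2.2: 24 dyads, 30% attrition, target of 30 to 50 participants. Loss: 0.30 × 24 = 7.2, stated as 7. Remaining: 24 − 7 = 17 dyads, or 34 people, which is within the target. The plan's figure reproduces.

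**2. Share of pilot places held by co-creators.** Inputs: 12 grandchildren and 12 grandparents per trajectory (read here as 12 dyads), two trajectories, 24 pilot places.
- Same people in both trajectories: 12/24 = 50%.
- Wholly different people, all continuing: 24/24 = 100%. This end fits poorly with the separate pilot recruitment that section 2.2.2 plans, so it is a limit only.

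**3. Ceiling on pre-exposed RCT dyads.** Co-creators sit inside the 24 pilot dyads, so at most 24 dyads have been exposed. If all entered the RCT: 24/54 = 44%, or 24/3 = 8 expected per arm of 18. If 12 entered: 12/54 = 22%, or 4 per arm. If only the 17 dyads expected to finish the pilot entered: 17/54 = 31%. The documents give no basis for predicting how many would enter.

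**4. What that could do to the contrast (illustration).** Let q be the share of dyads pre-exposed, Δ the full programme effect, and r the part of Δ an exposed dyad still carries at RCT baseline. Assume an exposed dyad in an active arm can gain only the remaining (1 − r)Δ, and an exposed control stays where it is. The active-minus-control difference in change is then

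(1 − q)Δ + q(1 − r)Δ = (1 − qr)Δ.

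For the power effect, the RCT's base size is reproduced first: f = 0.15 (read as Cohen's f; the metric is not stated), 3 groups, 3 measurements, alpha 0.05, correlation ρ = 0.5 (assumed), repeated-measures group-by-time interaction. With N = 90, λ = f²·N·m/(1 − ρ) = 0.0225 × 90 × 3/0.5 = 12.15, with 4 and 174 degrees of freedom. Power is 0.796, in line with the stated 80%. Replacing f by f(1 − qr):

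| q | r (assumed) | 1 − qr | Power at N = 90 |
|---|---|---|---|
| 0.22 | 0.25 | 0.945 | 0.74 |
| 0.22 | 0.50 | 0.89 | 0.68 |
| 0.44 | 0.25 | 0.89 | 0.68 |
| 0.44 | 0.50 | 0.78 | 0.55 |

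The documents do not give r. Six pilot sessions are 25% of a 24-session programme and 50% of a 12-session one, but treating effect as proportional to sessions with no decay is itself an assumption. If r is near zero, nothing is lost.

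**The case against.** The strongest reply concerns the RCT half. The article is condensed, and its list of RCT criteria is plainly a summary: it omits even the 6-to-10 age range from section 2.2.1. Where the authors want participants carried forward, as in the pilot, they say so; the RCT text has no such phrase. The full protocol may bar previous participants. This stands as a limit: enrolment of exposed dyads is allowed by the text shown, not announced by it. It does not remove the point, because the article states that the criteria are the same as before, and under those criteria a pilot dyad qualifies.

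On the pilot, keeping end-users in the refinement step suits a co-creation design, no go/no-go threshold is set, new dyads are to be recruited, and experts and a stakeholder focus group also contribute. That stands too. Feasibility is not judged by co-creators alone, and requiring an all-new pilot would be a preference. Nor is there an evident reason why co-creators would distort the choice of accelerometer or of cognitive tests. What remains is that pooled appeal, feasibility and recruitment results mix two different populations.

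A reader might also infer that pilot drop-out determines the RCT sample size, or that the same schools will be approached. The documents support neither. The RCT's 20% attrition and its effect size come from cited references. The recruitment strategy is shared, but the schools are not said to be the same, and the RCT area extends to the neighbourhood of Ghent.

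**Conclusion.** The point holds in a limited form. The overlap between co-creation and pilot is explicit: 12 of 24 dyads if one group follows both trajectories, more otherwise. Pooled enjoyment, feasibility and recruitment results are therefore likely to be optimistic for new families. That direction is a judgement, and the documents do not allow its size to be estimated.

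For the RCT, the stated criteria permit pre-exposed dyads in every arm. It is tempting to read this as 44% of the trial being contaminated, with the effect cut by 22% (0.44 × 0.5). The documents do not support that: 44% needs every pilot dyad to enter, and the 50% carry-over is unsupported. Randomisation would also balance previous exposure across arms in expectation, so the main consequence is attenuation and extra noise rather than a bias favouring one arm. At most 24 of 54 dyads are affected. The power figures show only that the loss could matter under the stated assumptions.

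**What to change.** **RCT eligibility** (section 2.2.3, Participants and Sample Size; repeat in Appendix A, item 4): state that dyads who took part in the co-creation sessions or the pilot are not eligible for the RCT. The documents give no reason to extend this to other household members.

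**Pilot** (section 2.2.2, Participants and Sample Size): keep co-creators if they are wanted for refining content, but summarise them separately and base the conclusions on appeal, feasibility and recruitment on dyads new to the project. State how many new dyads will be recruited, since these conclusions would have no basis if co-creators filled every place.

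**Cost.** The local recruitment pool shrinks by about 24 dyads. The pilot's feasibility figures also rest on fewer people: with 12 co-creation dyads, 12 new dyads remain, or 24 people before drop-out, which is below the 30 to 50 the pilot aims for. The authors would have to accept that loss of precision or recruit more new dyads. Both text changes are simple before recruitment starts.

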##### Data Analysis

Multilevel linear analysis in R will be used to estimate the between and within subject effects on PA, cognitive functioning, psychosocial well-being, and the quality of the familial relationship in grandchildren and grandparents. The mediating role of co-PA in the relationship between PA, cognitive functioning, psychosocial well-being, and the quality of the family relationship will be statistically checked in R using structural equation modelling (path analysis). Open-ended questions will be conducted using content analysis in SPSS (i.e., creating a code tree and looking for themes in the responses) [64].

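### The rule that a whole dyad leaves when one member drops out is stated in the pilot section with unclear reach; the RCT's 20% attrition does not fit it, and applying it there would discard usable individual data

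*Protocol article*

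**What the plan says.** All references are to the protocol article.

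- **Section 2.2.2, Participants and Sample Size (pilot).** The rule reads: "if one grandchild or grandparent drops out, this implies that the whole dyad will be excluded from the study". It is given as the reason for the attrition allowance: "A projected attrition rate of 30% instead of 20% has been chosen because we have taken into account" this dyad rule. The allowance is 7 of 24 dyads.
- **Section 2.2.3, Participants and Sample Size (RCT).** The power analysis gives about 45 dyads (90 people) for 80% power, with effect size 0.15, alpha 0.05, three groups and three measurements. The next step begins "Assuming an attrition rate of 20"%, and ends at 54 dyads (108 people), 18 dyads per arm. The dyad rule is neither repeated nor withdrawn.
- **Section 2.2.3, Data Analysis.** "Multilevel linear analysis in R will be used to estimate the between and within subject effects" on all four outcome domains. Nothing limits the model to complete dyads.
- **Section 2.2.3, Outcome measures.** Accelerometry, CANTAB and the questionnaires are collected from each person. Some questionnaires exist for one generation only: PedsQL for the children; WEMWBS, 4DSQ and SELSA for the grandparents.
- **Section 2.2.5.** The word study is used there for all three parts of the project: co-creation, pilot and RCT.

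**The concern.** Two things do not fit together.

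First, the attrition figures. The pilot runs for about six weeks, and 20% is rejected there because losing one person loses the pair. The RCT also counts its sample in pairs and runs for 24 weeks, with follow-up at 36 weeks, yet it uses 20%. The reason given for 30% is the paired structure, which both stages share.

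Second, the rule itself. A grandparent's CANTAB score or accelerometer record stays valid when the grandchild stops, and the reverse. Only co-PA needs both people. A multilevel model can use a dyad with one member observed, so the planned analysis does not require the exclusion.

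If the rule were carried into the RCT, people would be removed after allocation because of someone else's decision. The active arms attend 12 or 24 sessions and the control arm attends none, so drop-out may differ by arm. In that case the exclusion could bias the comparison as well as shrink the sample.

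**Working it through.** **Pilot figure.** 0.30 × 24 = 7.2, so 7 dyads are lost and 17 dyads (34 people) remain. This reproduces the stated allowance.

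**RCT figure.** The inputs from the article are effect size 0.15, alpha 0.05, k = 3 groups and m = 3 measurements. Two inputs are assumed because the article does not give them: the effect size is Cohen's f, and the correlation between repeated measures is ρ = 0.5. The test is the within-between interaction in a repeated-measures ANOVA:

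- λ = f² × N × m / (1 − ρ)
- df₁ = (k − 1)(m − 1) = 4
- df₂ = (N − k)(m − 1)

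For N = 90, λ = 0.0225 × 90 × 3 / 0.5 = 12.15 and df₂ = 174, which gives power 79.6%. This matches the stated 80%. Like the article's n = 90, it treats the two members of a dyad as independent observations.

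**What the rule would cost in the RCT.** Let q be the drop-out probability per person. If partners drop out independently, dyad loss L = 1 − (1 − q)², so q = 1 − √(1 − L). From 108 people:

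- people who can still be measured = 108 × (1 − q)
- people kept under the rule = 108 × (1 − L)

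| Dyad loss L | q | Still measurable | Kept under the rule | Power (ρ = 0.5) |
|---|---|---|---|---|
| 20% (RCT figure) | 10.6% | 96.6 | 86.4 | about 83% vs 78% |
| 30% (pilot figure) | 16.3% | 90.4 | 75.6 | about 80% vs 71% |

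If partners always leave together, q = L, the two counts are equal and nothing is lost. Among non-negative concordances, independence is therefore the upper end of the cost.

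**Sensitivity to ρ.** For 90 versus 76 people, power is 63% versus 55% at ρ = 0.3, and 96% versus 92% at ρ = 0.7.

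**The same comparison in the pilot.** At 30% dyad loss with independent drop-out, 48 × (1 − 0.163) ≈ 40 people could still be measured, against 34 kept under the rule.

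**The case against.** The strongest reply is that the rule belongs to the pilot and does no harm there. The pilot section says "There will be 2 groups of 12 dyads" and describes no random allocation. Its aim is practical: "The purpose of this portion of the study will be to finetune the programs and recruitment strategies to optimize the RCT". It claims no power and relies on a rule of thumb: "The required sample size for a pilot study is between 30 and 50 participants". The 34 people left after the budgeted loss are within that range. All of this stands. A reader might infer that the pilot suffers a post-randomisation exclusion or an unplanned loss of power, and the document supports neither.

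A reader might also infer that the RCT is committed to discarding half-dyads. The article does not say so. The RCT section omits the rule and uses the very rate the pilot rejected, and the rule may only mean that a lone member cannot continue in joint sessions. Its reach rests on the wording (the study, a term used elsewhere for all three parts) and on the shared paired design. That is enough to make the reach unclear, but not to settle it.

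On size, reading the 20% as drop-out per person would give 36% dyad loss (1 − 0.8²), with 86 versus 69 people and power 77% versus 66%. However, the RCT section applies its 20% to the dyad count (45 × 1.2 = 54), so that larger gap is not the natural reading. Joint attendance also makes concordant drop-out plausible, which lowers the cost further.

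Finally, Section 3 names co-PA as the primary outcome, and co-PA needs both members. Keeping the remaining member recovers nothing for that outcome. Sections 2.1.1 (Step 4) and 4 also count cognitive functioning as primary, and there the gain is real.

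**Conclusion.** The point holds as an inconsistency with a conditional consequence. The exclusion rule is written down, its scope is unclear, and the RCT's 20% does not follow from the reasoning that produced the pilot's 30%. If the rule governs the RCT, it drops people with usable individual outcomes for a reason that may differ by arm.

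The cost in power lies between nothing (fully concordant drop-out) and, under independent drop-out, about 5 percentage points at 20% dyad loss or 9 points at 30%. These figures assume f = 0.15 is Cohen's f, ρ = 0.5 and independent dyad members. They indicate size and direction only. The possible bias cannot be quantified from the document. In the pilot the cost is modest and already budgeted.

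**What to change.** 1. **RCT.** State that when one member of a dyad stops, the other is still invited to all measurements and is analysed in the allocated arm, in the multilevel model with dyad as a random effect. Only co-PA becomes missing.
2. **Pilot.** Likewise keep the remaining member's data, without reference to randomisation.
3. **Attrition.** Say whether the dyad rule applies in the RCT. State the expected loss per person and per dyad, align the RCT figure with the pilot's reasoning, and restate the power that follows at 54 dyads, rather than enrolling more.

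The cost is a few sentences in the protocol and some extra measurement visits for remaining members. The change does not recover co-PA data, so missing co-PA still has to be handled separately.
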